## Abstract

**Background:**

Despite the fact that the cost-effectiveness of robot-assisted radical cystectomy (RARC) is not yet proven, and open radical (ORC) cystectomy is recommended as the standard of care in patients with high-risk non-muscle-invasive and muscle-invasive bladder cancer, the use of RARC is still increasing. The objective of the current ongoing comparative effectiveness trial therefore is to study the (cost-)effectiveness of RARC compared to ORC, both in terms of objective (complication rates, oncological outcomes) and patient-reported (health-related quality of life) outcome measures.

**Methods:**

This study is designed as a non-randomized, multicentre comparative effectiveness trial.

Centres with an annual caseload of > 20 radical cystectomies can include patients after informed consent has been given. Centres that perform RARC must have passed the (initial) learning curve of 40 cases. A total of 338 (2 × 169) patients will be enrolled from 23 participating centres (12 ORC, 10 RARC and 1 LRC). Follow-up visits will be scheduled at 1, 3, 6 and 12 months. During each follow-up visit, clinical data and health-related quality of life questionnaires will be administered. Costs will be studied using a monthly resource usage questionnaire. Impact on complications and quality of life will be calculated as the average difference between the groups with 95% confidence intervals, adjusted for potential baseline differences by means of propensity score matching.

**Discussion:**

This study aims to contribute to the development of evidence-based guidelines regarding the most cost-effective surgical technique for radical cystectomy.

**Trial registration:**

Nederlands Trial Register/Dutch Trial Registry, trial identifying number: NTR5362. Registered on 14 August 2015. (http://www.trialregister.nl/trialreg/admin/rctview.asp?TC=5362).

## Background

Radical cystectomy with pelvic lymphadenectomy and urinary diversion is the standard of care for both high-risk non-muscle-invasive bladder cancer and muscle-invasive disease [1]. This surgery is complex and associated with considerable postoperative morbidity, including major and minor complications with probabilities ranging from 13 to 67% [2–6]. Complications may lead to extra costs, prolonged hospital stay, additional interventions, a reduced quality of life, and a longer time before patients may return to normal activities.

Currently, there are two main surgical techniques to perform a radical cystectomy: robot-assisted (RARC) and open surgery (ORC). ORC is the recommended treatment according to European guidelines, but RARC has been suggested to improve the perioperative morbidity without compromising oncological efficacy, and the percentage of hospitals and surgeons performing RARC is increasing steadily [7]. For example, 11 out of 69 (14.4%) Dutch centres performed RARC in 2014, and in 2016 24% of all radical cystectomies were performed robot assisted [8]. In the USA, the use of robot assisted technique has increased from 1% in 2004 to 13% in 2010 [9]. High-level evidence of methodologically sound clinical studies that compare both treatments is, however, lacking. Furthermore, direct costs of robotic surgery are expected to be higher than for open surgery, so investment in this technology can only be justified when additional costs are balanced by a significant benefit regarding patient outcomes.

### Existing knowledge

At the time we designed this study (2015), two systematic reviews (both including 105 studies) had been reported. [2, 10] Novara et al. reported on perioperative outcomes and complications after RARC, whereas Yuh et al. reported on oncologic and functional outcomes after RARC. Ninety-three of the 105 studies reported perioperative outcomes and complications of RARC; including 23 comparative studies and 70 surgical series. Most of the surgical series were retrospective single centre studies and only three randomized trials were found.

The overall results showed shorter operative time for ORC, whereas blood loss and hospital stay were better with RARC. Moreover, 90 day complication rates of any grade and grade 3 complications were lower for RARC, whereas high-grade complication and mortality rates were similar [2] Analyses showed no significant difference between RARC and ORC in lymph node yield and rates of positive surgical margins [10]. Very limited data were available with respect to functional outcomes and quality of life. According to both authors, the most relevant limitations of their systematic reviews were the quality of the included studies, the small study populations, the retrospective nature of most series, the short follow-up period, and the lack of standardized definitions [2, 10]. This lack of methodologically sound data precludes a definite conclusion about the effectiveness of RARC versus ORC.

Up to now, four randomised trials [11–14] have been reported and two others are ongoing (RAZOR [15] and iROC (ClinicalTrials.gov identifier: NCT03049410). Shen et al. [16] performed a meta-analysis of these 4 RCT’s [11–14] and presented evidence for a benefit of estimated blood loss, time to diet, similar perioperative complications and oncological outcomes, but a longer operative time in RARC. Furthermore, in the largest trial [13] surgeons performing RARC were still in their learning curve, and another trial only included 20 patients per arm and potential surgeon bias (i.e. there was a different surgeon for each technique) could not be precluded [14].

The two ongoing trials, i.e. RAZOR [15] and iROC, comprise multi center trials. RAZOR is a multi-institutional, randomized, non-inferiority, phase III trial, which aims to enrol 320 patients from 15 participating centres in the USA. They will study oncological outcomes, complications and quality of life of RARC compared to ORC. The primary endpoint is progression-free survival after 2 years. A potential limitation of the RAZOR trial might be the RARC learning curve, as surgeons must have performed only more than 10 RARCs in the past year. The learning curve of RARC is, however, estimated to be between 16 and 30 cases [17–19]. iROC is a prospective multicentre randomised controlled trial comparing the outcomes of intracorporeal RARC (iRARC) with ORC, which aims to enroll 320 patients. The primary outcomes (functional recovery and return to normal activities) will be measured 90 days post-surgery.

### Need for a comparative-effectiveness trial

As described above, all trials performed so far have been limited by sample size and design, or by their application of RARC with extra-corporeal reconstruction. We have chosen for a comparative effectiveness study since observed effectiveness will depend on the complex decision-making process of clinicians selecting therapies, their experience with the technique under study, and on the decisions and actions of patients, including whether they accept or prefer a certain surgical technique. The impact of these issues on effectiveness may be difficult or impractical to assess in a traditional RCT, in which treatment assignments are randomized and may therefore lead to a bias due to the expertise of the surgeons in a center.

### Objective

The objective of the current ongoing comparative-effectiveness trial is to study the effectiveness of RARC as compared to ORC in patients with bladder cancer and an indication for radical cystectomy in terms of complication rates, health related quality of life, and disease free survival.

## Methods

### Design

This study is designed as a non-randomized, multicentre comparative effectiveness trial. Patient recruitment is currently being conducted at urology outpatient clinics in five academic tertiary referral centres and eighteen referral centres in the Netherlands. A multicentre approach was chosen to obtain the desired power and to assure representativeness of our sample to the target population. Each centre will perform either RARC or ORC. Centres that perform both RARC and ORC can only participate if they do not select a technique based on patient characteristics, other than described in the exclusion criteria. Only high volume centres (> 20 radical cystectomies per year) can participate in the study. To prevent learning curve bias, only centres that have performed at least 40 RARCs can participate.

### Characteristics of participants

#### Inclusion criteria

Patients eligible for the trial must comply with all of the following:Eighteen years or older.Oncological indication for radical cystectomy.Histologically proven primary muscle invasive transitional cell carcinoma or therapy resistant high-risk non muscle-invasive bladder cancer (CIS, refractory pTa-1).Tumour is considered non metastatic (cT1a-cT4a, N0 M0) at the time of inclusion. Patients with N+ status may receive neoadjuvant chemotherapy, but can only be included in the study when preoperative scans show N0.Able to fill in Dutch questionnaires.Provide written informed consent.

#### Exclusion criteria

When a patient meets one of the following exclusion criteria, they will be excluded from participation:Previous major abdominal surgery (i.e. existing stomata, status after low anterior resection of the rectum or rectal amputation, status after open aortabifemoral graft, status after right hemicolectomy).Morbid obesity (BMI ≥ 40 kg/m2).Radical cystectomy is performed in combination with a nephrectomy or a partial colon resection.Pregnancy.

### Interventions

Overall, the surgical techniques for ORC or RARC are standardized procedures. Radical cystectomy with pelvic lymphadenectomy with diversion will be performed in all cases. If the formation of a neobladder is oncologically safe and technically feasible, patients can choose between an ileal conduit and a continent urinary diversion (neobladder). For RARC, one centre performs an extracorporeal technique, whereas all other centres perform a total intracorporeal reconstruction.

The peri-operative protocol has been standardized for all participating centres, including a fast track (ERAS) protocol. All centres are asked to follow the RACE-ERAS protocol, based on the current international guidelines and best available evidence. An identical protocol is used for RARC and ORC, to prevent bias due to different perioperative protocols. Table 1 presents the RACE-ERAS protocol used for this study.

**Table 1 Tab1:** ERAS protocol used for RACE study

Item	Standard	Optional
1. Pre-operative: extensive counselling patient	✓	
2. Correction anaemia (Hb ≥ 6 mmol/l)	✓	
3. Pre-operative consult dietary specialist		✓
4. Quit smoking		✓
5. Physical exercise before surgery		✓
6. Pre-operative enema: 12 h before surgery (in case of constipation)		✓
7. Pre-operative: High calorie fluids, until 2 h before surgery	✓	
8. Pre-operative: solid food until 6 h before surgery	✓	
9. Pre-operative: clear fluids, until 2 h before surgery	✓	
10. Epidural analgesia (thoracal) until max 72 h after surgery	✓	
11. Antibiotic prophylaxis, one-shot pre-operative Cefazoline (≤80 kg 1 g; > 80 kg 2 g) + Metronidazole (500 mg). May be repeated if the operation time is longer than the half-life	✓	
12. Anaesthetic considerations Normothermia, Goal directed fluid therapy, normovolemia, short acting sedatives, minimalize opioids.	✓	
13. Post-operative: nasogastric tube removed directly after surgery	✓	
14. Post-operative: start laxantia post-op day 1	✓	
15. Post-operative: chewing gum		✓
16. Post-operative: standard anti-emetica	✓	
17. Post-operative: start mobilisation 6 h after surgery	✓	
18. Post-operative: fluid diet until first stool	✓	
19. Post-operative: Thrombosis prophylaxis for four weeks with ‘low molecular weight heparin’ = LMWH (Fraxiparine 0,6 cc)	✓	

### Outcomes

#### Primary endpoint

The primary outcome measure comprises 90 days complications, according to the Clavien-Dindo classification [20].

#### Secondary endpoints

Secondary outcomes comprise perioperative morbidity and mortality, 30 days and 1 year complications, health-related quality of life, disease free survival, time to return to normal activity, blood loss and transfusion parameters, operating time, hospital and intensive care stay, oncological outcomes, and costs.

#### Patient reported outcomes

Health-related quality of life is measured at baseline (pre-operatively) and post-operatively at 1, 3, 6, and 12 months using three quality of life questionnaires: Functional Assessment of Cancer Therapy–Bladder cancer Cystectomy (FACT-Bl-Cys, formerly FACT-VCI), Bladder Cancer Index, and the 5-level version of the EuroQol 5D (EQ-5D-5 L).

The FACT-Bl-Cys questionnaire is a disease and treatment-specific tool for assessing quality of life following radical cystectomy and urinary diversion [21]. It includes 42 questions dealing with general domains (physical, social/family, emotional and functional well-being) plus 17 additional items covering urinary, sexual, and bowel function. The Bladder Cancer Index is developed for patients who are diagnosed with bladder cancer and covers a broad range of health and quality of life, including three domains, namely urinary, bowel and sexual functioning, containing 14, 10 and 12 items, respectively [22]. The EQ-5D-5 L consists of a descriptive part and a visual analogue scale (VAS) [23]. The descriptive part comprises the following five dimensions: mobility, self-care, usual activities, pain/discomfort, and anxiety/depression. The VAS records the respondent’s self-rated health on a vertical scale ranging from 0 (worst imaginable health state) to 100 (best imaginable health state).

Resource use will be assessed using the RACE healthcare usage questionnaire, which is based on the iMCQ [24] (to assess medical consumption such as hospital visits, medication use and domestic help) and the iPCQ (to measure absence from work due to illness) [25]. This questionnaire will be completed at baseline (pre-operatively) and every month afterwards. It records resource use, such as doctor’s visits, medication, hospital admissions, and out-of-pocket expenses such as over-the-counter drugs. Additionally, travelling time to the outpatient clinic and related costs are asked for. Where relevant, (missing) entries will be verified by data from the medical records.

#### Clinical outcomes

Perioperative and postoperative measures (e.g. blood transfusion rates, intraoperative fluid requirements, operative time, length of hospital stay and analgesic requirement) are prospectively recorded. Operating time is defined as the skin-to-skin operating time in minutes, not including anaesthetic preparations as these might differ between the participating centres. Total operating room occupation time is also measured.

Pathological data is obtained from pathology reports after surgery with particular emphasis on surgical margin status, total number of lymph nodes removed and their involvement with cancer, as well as pathological stage of the tumour. A standardized form will be used to collect all information pertaining to specimen processing and staging by the participating institutions. In addition, since centres are obliged to complete the national urologic database, the Dutch Urological Association can and will provide us with export files for each RACE participant, which will subsequently be imported in the eCRF (electronic Case Report Form).

### Participant timeline

Timeline is depicted in Fig. 1. Treating urologists in the participating centres will recruit patients that fulfil the in- and exclusion criteria. Information is given about the rationale and the design of the RACE study. Potential participants will receive both the information letter and the informed consent form. Patients will have sufficient time to consider participation. If they agree to participate, informed consent will be signed. Once patients signed informed consent, contact information will be transmitted to the coordinating researcher. Patients will be operated in their own centre within 4 to 6 weeks; from the moment they signed informed consent.

**Fig. 1 Fig1:**
[figure not shown]
Flowchart RACE study

Patients are asked to fill in 3 quality of life questionnaires at five different time points: before the operation, and then 1, 3, 6 and 12 months after surgery, which will take about ten minutes per questionnaire. In addition, patients are asked to fill in a cost questionnaire monthly, which will take approximately less than five minutes.

Clinical data are registered in a central validated database (eCRF, Research Manager) by (local) researchers. Clinical consultations are scheduled 1, 3, and 12 months after surgery. The data acquisition is presented in Table 2.

**Table 2 Tab2:** Standard Protocol Items: Recommendations for Interventional Trials (SPIRIT) flow diagram of study enrolment, interventions and assessments

	Study period					
	Enrolment	Allocation	Post-allocation			Close-out
Timeline	4–6 weeks before Radical Cystectomy	Radical Cystectomy	1 m	3 m	6 m	12 m
Timepoint	-t_1_	0	t_1_	t_2_	t_3_	t_4_
Enrolment:						
Eligibility screen	X					
Informed consent	X					
Intervention: RARC or ORC		X				
Assessments:						
Quality of Life	X		X	X	X	X
Patient based healthcare usage	X	Monthly				
Clinical data			X	X		X

### Sample size

Based on an overall complication percentage of 65% in the ORC [3] a sample size of 338 (2 × 169) patients is required (power 80%; alpha 5%) to detect a decrease in the overall complication rate of 15%, i.e. from 65 to 50%.

### Recruitment

Urologists from 23 Dutch centres are involved in patient recruitment. Patient information has been designed in close cooperation with the patient society, i.e. representatives of the Bladder Cancer Patient Society “Leven met Blaas- of Nierkanker” are full members of the RACE project team. Both the support of the Dutch Urology Association and Bladder Cancer Patient Society “Leven met Blaas- of Nierkanker” will help us to include sufficient patients in the trial. Screening and recruitment will continue until the target population (*n* = 338) is achieved.

### Data collection methods and data management

Questionnaires will be administered web-based or paper-based, processed and stored digitally using a validated data management system (eCRF, Research Manager). Participant application forms (provided by urologists in participating centres), medical history, and clinical data will be registered, processed and stored using eCRF Research Manager. Data will be handled according to the Dutch law (Dutch Data Protection Act). Data will be anonymized by a unique identification number.

### Statistical methods

#### Outcomes

Effects on complications, disease free survival, blood transfusion and organ injury will be calculated as rate differences with 95% confidence intervals. Effects of surgery on quality of life, pain after surgery, time to return to full activity, operating time and hospital stay will be calculated as mean differences with 95% confidence intervals. All analyses will be performed on an intention-to-treat basis. To account for potential confounders (including confounding by indication), we will use both multivariate regression models and propensity score methods. Furthermore, a rule-out approach will be used for sensitivity analysis [26] to illustrate how strongly a single unmeasured binary confounder would have to be associated with both the intervention and the end point to fully explain eventual significant findings. Multiple imputation using 10 imputed data sets will be used to handle missing data.

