## Discussion

Radical cystectomy with pelvic lymphadenectomy and urinary diversion is the standard of care for both high-risk non-muscle-invasive bladder cancer and muscle-invasive disease [1]. Due to improved anaesthesia, better surgical techniques, and centralization of care in high volume centers, reduction in morbidity and mortality has occurred in recent years. Furthermore, the ERAS protocol has also helped to reduce the length of stay and complications [29]. RARC has been suggested to potentially improve the perioperative morbidity. However, high-level evidence of any benefit from RARC over ORC of methodologically sound clinical studies is lacking. This may reflect the complex nature of this procedure as well as the complex decision-making process of clinicians selecting therapies, their experience with the technique under study, and on the decisions and actions of patients, including whether they accept or prefer a certain surgical technique. The impact of these issues on effectiveness may be difficult or impractical to assess in a traditional RCT, in which treatment assignments are randomized and may therefore lead to a bias due to the expertise of the surgeons in a center. So far, four prospective trials have compared RARC with ORC, but each of them has been limited by sample size, design, or their application of RARC with extra-corporeal reconstruction [11, 13, 14, 30].

A comparative effectiveness trial aims to provide high-quality evidence to help patients and clinicians make informed clinical decisions and to assist health systems in improving the quality and cost-effectiveness of clinical care. The major strength of our design is that we compare the preferred treatment strategy (RARC versus ORC) of several centers. Not only the surgeon, but also the team and caseload will influence the outcome for patients. With this comparative effectiveness study we compare outcomes of standardized procedures performed by surgical teams of 23 hospitals (12 ORC, 10 RARC and 1 LRC). The results will provide a valid estimate of the real effectiveness in daily clinical practice. Furthermore, we will be able to study whether the distribution of robotic systems over hospitals and patient allocation to these hospitals is indeed more or less random. Nevertheless, we will also perform propensity score analyses to adjustment for potential confounding (by indication).

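### Technique is largely set by the centre, but the sample size assumes independent patients and no stated analysis accounts for centre

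*Protocol article*

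**What the plan says.** The Design section sets technique by hospital: "Each centre will perform either RARC or ORC". It then makes a conditional exception: "Centres that perform both RARC and ORC can only participate if they do not select a technique based on patient characteristics", apart from the exclusion criteria. The number of such centres is not given. The Abstract and the Discussion list all 23 centres under a single technique: 12 open (ORC), 10 robotic (RARC) and 1 laparoscopic.

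The Discussion presents the comparison of the centres' preferred strategies as a strength and adds: "Not only the surgeon, but also the team and caseload will influence the outcome for patients".

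The Sample size section asks for 338 patients, 169 per group, at 80% power and 5% alpha, "to detect a decrease in the overall complication rate of 15%, i.e. from 65 to 50" per cent. It mentions no allowance for clustering.

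For the analysis, the Outcomes part of Statistical methods says: "Effects on complications, disease free survival, blood transfusion and organ injury will be calculated as rate differences with 95% confidence intervals". Quality of life, operating time, hospital stay and similar outcomes get mean differences with 95% intervals. Multivariate regression and propensity score methods are named to deal with confounders; the Abstract specifies propensity score matching. The economic evaluation uses a bootstrap without stating its resampling unit. None of these places mentions a centre term, a random effect, a robust variance or resampling of centres.

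**The concern.** Where a hospital uses one technique, the RARC versus ORC contrast is a contrast between groups of hospitals. If surgeon, team and caseload affect complications, as the article says, patients in the same hospital resemble each other, and the variance of the contrast contains a between-hospital part. An interval based only on the number of patients omits that part.

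The named adjustment methods do not restore it by default. Matching or regression on patient characteristics addresses imbalance between the groups; it does not remove correlation within hospitals. Ordinary fixed centre effects do not help either, because in a single-technique centre they are aliased with treatment. A valid interval therefore needs a deliberate choice.

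At stake is the primary comparison, which the Discussion intends to inform guidelines. Ordinary variation between two sets of hospitals could be read as an effect of the robot. In addition, 338 patients may carry less information than the stated power implies.

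**Working it through.** **Inputs from the article.** Complication rates 65% and 50%; 169 per group; power 80%; alpha 5% (sidedness not stated); 12 ORC and 10 RARC centres in the main comparison.

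**Assumed.** ICC 0.01 to 0.10, since none is given; all 338 patients in the 22 ORC and RARC centres; equal centre sizes; no centre performing both techniques.

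**Step 1: reproduce the stated size.** For a two-sided test of two proportions with pooled variance under the null:

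n = [1.96·√(2·0.575·0.425) + 0.8416·√(0.65·0.35 + 0.50·0.50)]² / 0.15²
= [1.370 + 0.582]² / 0.0225 ≈ 169.3 per group.

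This is 170 rounded up, against 169 stated; power at 169 is 79.9%. Other formulas give 167 (unpooled), 170 (arcsine), 183 (continuity-corrected) and 134 (one-sided). The stated figure is thus the ordinary individual-patient result, with a design effect of 1.

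**Step 2: design effect.** Mean centre size m = 338/22 = 15.36, and DE = 1 + (m − 1)·ICC.

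- The correct interval is √DE times as wide as the independence interval.
- The actual error of a nominal 5% independence test is 2·[1 − Φ(1.96/√DE)].
- Power of an analysis that accounts for centre is taken at an effective 169/DE per group.

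| ICC | DE | Correct interval wider by | Actual error | Error, simulated | Power at 338 |
|---|---|---|---|---|---|
| 0.01 | 1.14 | 7% | 6.7% | 7.0% | 74% |
| 0.02 | 1.29 | 13% | 8.4% | 8.9% | 69% |
| 0.05 | 1.72 | 31% | 13.5% | 13.7% | 57% |
| 0.10 | 2.44 | 56% | 20.9% | 21.5% | 43% |

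Example for ICC 0.05: DE = 1 + 14.36·0.05 = 1.718; √1.718 = 1.311; 1.96/1.311 = 1.495, which gives 13.5%; effective n = 169/1.718 = 98.4 per group, which gives 57% power.

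The simulation drew beta-binomial outcomes in 12 and 10 centres of near-equal size, 169 patients per group and a common rate of 65%, with 40,000 runs per ICC. With ICC 0 it returned 5.1%, as it should.

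**Step 3: sensitivity.**

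- Unequal centre sizes, with an assumed coefficient of variation of 0.5 and DE = 1 + [(1 + 0.5²)·m − 1]·ICC: for ICC 0.01 to 0.10 the error is 7.1% to 24.3% and power 73% to 38%.
- Spreading 338 patients over all 23 centres (m = 14.7) changes little: error 6.6% to 20.3%, power 75% to 44%.
- The power figures use normal quantiles. A small-sample correction for 22 centres would lower them somewhat further.

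**The case against.** A reader might infer that every planned interval treats patients as independent. The article does not support that. It gives no variance method; its regression models could contain a random centre effect or use robust variance, and its bootstrap could resample centres. The full protocol and any statistical analysis plan are not shown, and a journal article may leave the variance estimator to them. This part of the objection stands, so the statement about the intervals must be conditional.

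A reader might also infer that the whole contrast lies between centres. The Design section conditionally admits centres performing both techniques, and comparison within such centres would reduce the design effect. Their number is unknown, although the centre count lists none as mixed. Centre-level allocation is therefore the main rule, not an absolute one.

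Thirdly, the ICC could be small. Centres must perform more than 20 cystectomies a year, RARC centres must have done at least 40, and one ERAS protocol applies to both techniques. These features should limit variation between centres, but they do not show that it is zero, and the article itself expects team and caseload to matter. At ICC 0.01 the loss is modest; the large figures need an ICC near 0.10.

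The objection does not remove the sample size. There the assumption can be checked, and it is independence. Nor is the rest merely omitted detail: the article specifies 10 imputations and a sensitivity analysis for one unmeasured confounder, yet names nothing for the main statistical consequence of its own allocation by centre.

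**Conclusion.** The point holds in conditional form. Independence is demonstrably built into the sample size, technique is largely allocated by centre, and no stated analysis accounts for centre. If the intervals are computed without centre and the ICC exceeds 0, they are too narrow and the false-positive risk exceeds 5%.

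The size rests on an assumed ICC and on the equal-size, no-mixed-centre simplification. Unequal centre sizes would worsen the figures; mixed centres would improve them. The article does not support an unconditional claim that the primary 95% interval lacks 95% coverage.

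**What to change.** State in the analysis plan, before analysis, that all RARC–ORC comparisons account for centre:

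- For the primary endpoint, use a model with a random centre intercept, or GEE or cluster-robust variance with a small-sample correction suited to about 22 centres. Standardise the result to an adjusted risk difference, so that the planned effect measure is kept.
- Apply the same principle to the other binary and the continuous outcomes, including the propensity score analyses.
- In the economic evaluation, resample whole centres in the bootstrap.
- Say how many centres perform both techniques and how they enter the model.
- Report the estimated ICC, and restate the power at 338 patients over a range of ICC values.

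The cost is wider intervals and a lower stated power. No extra patients or change to conduct is needed. Centre should already be identifiable, since participating centres supply the application forms and monitoring is organised per centre.

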### Trial status

Recruitment started in March 2016 and is currently ongoing. A total of 273 patients were enrolled by mid- March 2018 and we expect to finish inclusion by the end of 2018. One year followup of last patient and statistical analyses expected by the end of 2019.

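### Time to return to activity is planned as an ordinary mean difference, although patients who die or have not returned by 12 months have no return time to average

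*Protocol article*

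**What the plan says.** Time to return to activity is a secondary endpoint, listed with others as "disease free survival, time to return to normal activity, blood loss and transfusion parameters". The Outcomes part of Statistical methods groups it with continuous measures: "time to return to full activity, operating time and hospital stay will be calculated as mean differences with 95% confidence intervals".

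Three further statements bear on how that mean would be formed:

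- Analysis set: "All analyses will be performed on an intention-to-treat basis".
- Missing data: "Multiple imputation using 10 imputed data sets will be used to handle missing data".
- Confounding: "we will use both multivariate regression models and propensity score methods".

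Follow-up is a fixed year per patient. The abstract says "Follow-up visits will be scheduled at 1, 3, 6 and 12 months", and Trial status says "One year followup of last patient and statistical analyses expected by the end of 2019". The article names no time-to-event or competing-risk method for this outcome. It does not say how a patient enters the mean who dies or is still not back to activity at the last visit.

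**The concern.** A mean difference suits a quantity that every patient has. Operating time is one. Time to return to activity is not, for two reasons. Return after 12 months is not observed, so those times are censored. Death rules out return, and deaths are expected because mortality is itself a listed secondary outcome.

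The stated text suggests two ways of completing the mean, and both are unsatisfactory:

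- **Leaving out patients without a return time.** This conflicts with the intention-to-treat statement and conditions on a post-surgical outcome.
- **Imputing a return time.** The model would be fitted to observed times, all of which come from returners, so a missing-at-random model supplies returner-like values. For a patient who died there is no value to recover.

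Either way, the estimate answers how quickly those who recovered did so. It does not answer how much time without normal activity each technique entails. Regression or propensity adjustment does not help, because the problem lies in how the outcome is defined for these patients.

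**Working it through.** **The plan's own figure.** The article gives no figure for this outcome. Its one design figure concerns 90-day complications: 65% against 50%, power 80%, alpha 5%. With the two-sided pooled formula, n per arm = [1.960·√(2·0.575·0.425) + 0.842·√(0.65·0.35 + 0.50·0.50)]² / 0.15² = 169.3. That is 169 or 170 per arm depending on rounding, and power at 169 is 79.9%. The stated 338 reproduces, and nothing below depends on it.

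**Illustration 1: inputs.** The 52-week horizon follows from the 12-month follow-up. All else is assumed, because the article gives no return times or non-return rates. Returners average 12 weeks (ORC) and 10 weeks (RARC). Non-return, including death, is varied from 5% to 15%.

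**Formula.** With r the proportion not returned by 52 weeks and m the mean among returners, the restricted mean time without return is R = (1 − r)·m + r·52. For ORC at 15%: 0.85·12 + 0.15·52 = 18.0. For RARC at 5%: 0.95·10 + 0.05·52 = 12.1. The difference among returners is 12 − 10 = 2.0 weeks in every row.

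| Non-return ORC / RARC | R, ORC | R, RARC | ORC − RARC (weeks) |
|---|---|---|---|
| 5% / 5% | 14.0 | 12.1 | 1.9 |
| 10% / 10% | 16.0 | 14.2 | 1.8 |
| 15% / 15% | 18.0 | 16.3 | 1.7 |
| 10% / 5% | 16.0 | 12.1 | 3.9 |
| 15% / 5% | 18.0 | 12.1 | 5.9 |
| 5% / 15% | 14.0 | 16.3 | −2.3 |

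With equal non-return the gap from 2.0 is 0.1 to 0.3 weeks. With unequal non-return it is larger. Starting from 5% in ORC (R = 14.0), the RARC advantage vanishes when 10 + 42r = 14.0, so r = 4.0/42 = 9.5%. An excess of about 4.5 points in RARC is enough.

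**Illustration 2: same speed in both arms.** Assume exponential return times with median 60 days among eventual returners, a 365-day horizon, and a further share q who die or never return.

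- The exponential mean is 60/ln 2 = 86.6 days, and the chance of exceeding 365 days is exp(−365/86.6) = 0.0148.
- The restricted mean with q = 0 is 86.6·(1 − 0.0148) = 85.3 days.
- The mean among those returning within the year is (85.3 − 365·0.0148)/(1 − 0.0148), about 81 days, whatever q is. The returners' difference is therefore about 0.
- In general R = 85.3 + q·(365 − 85.3), so each percentage point of imbalance adds about 2.8 days.
- With q of 10% against 5%, R is about 113 against 99 days, a difference of about 14. With 20% against 10% the difference is about 28 days.

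Simulation with 400,000 patients per arm gave the same values.

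**How plausible is an imbalance?** The Background section says complications may delay return to normal activities, and the trial is sized for a 15-point difference in complications. If that were the only route, a 5-point imbalance in non-return would need complications to raise the risk of non-return by 5/15 = 33 points. A 10-point imbalance would need 10/15 = 67 points. Some imbalance is plausible; the 15% against 5% case is at the severe end.

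**The case against.** The strongest reply is that the article is silent rather than wrong. It does not say that patients who die or do not return will be dropped or imputed. The imputation rule is general, and a mean difference could in principle be taken on times capped at 12 months. A reader might infer that the plan prescribes replacing the worst outcomes with typical ones; the text does not go that far. What stands against the reply is that the effect measure is stated, not left open. Nothing in the article points to a cap, and an analyst applying the sentence together with the general imputation rule would arrive at the returners' answer.

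The reply is right on size. Nothing in the article shows that non-return differs between arms, and the systematic review summarised under Existing knowledge found similar mortality with the two techniques. With balanced non-return the distortion is slight. It is also right on importance: return to activity is absent from the Objective section, and the article does not present faster return as a leading benefit of RARC.

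A reader might extend the criticism to disease-free survival, since "Effects on complications, disease free survival, blood transfusion and organ injury will be calculated as rate differences with 95% confidence intervals". The article does not support that extension. The planned adjustment for confounding means the difference is not shown to be a crude one. Under fixed 12-month follow-up a rate difference is a legitimate measure and can come from Kaplan-Meier estimates. If death counts as an event (assumed, as the article gives no definition), patients who die are not mishandled. Even a simple proportion does little harm. With assumed 12-month values of 75% and 80%, simulation gave differences of 4.8 to 5.1 points against a true 5.0 for equal loss of 0 to 10%. It drifted to 3.8 or 5.9 only when loss was 15% in one arm and 5% in the other. The horizon and the handling of early loss may properly sit in the full protocol or SAP.

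**Conclusion.** The point holds for one secondary outcome. An ordinary mean difference does not fit time to return to activity, and generic multiple imputation does not repair it, because patients who die have no return time and those not back by 12 months have only a lower bound.

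The consequence is conditional. If non-return and death are similar between arms, it is negligible: 0.1 to 0.3 weeks on a 2.0-week difference. If they differ, the returners' mean can understate the difference (2.0 against 5.9 weeks at 15% against 5%), hide it (about 0 against 14 to 28 days), or give the opposite direction (2.0 weeks in favour of RARC against 2.3 in favour of ORC). These figures rest on assumed return times and non-return rates; the article supplies neither. They show what the method can miss, not what this trial will find.

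The primary endpoint and the sample size are untouched, and no criticism of the disease-free survival analysis follows.

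**What to change.** For time to return to activity, replace the plain mean difference with:

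- the adjusted difference in restricted mean time without return to activity up to 12 months, with 95% confidence interval, counting non-returners and deaths to the 12-month horizon;
- the cumulative incidence of return by arm, with death as a competing event;
- a statement that return times are not imputed after death, and that patients alive but not back at 12 months count as not returned, not as missing.

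The planned regression and propensity score adjustment can be kept, for example through weighting or regression on pseudo-values. Patients lost while alive contribute their observed time. A mean among returners may be reported as a description if labelled as such. The endpoint should also carry one name: the secondary endpoint list refers to normal activity and the analysis section to full activity.

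The cost is a few lines in the analysis plan and slightly more analysis work with standard software. No new data are needed.
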